### Data collection and measures

Participants will complete three questionnaires: a baseline questionnaire at enrollment, a follow-up questionnaire 1 week after self-collection result delivery or appointment scheduling call, and an exit questionnaire 2 weeks after the participant attends a screening appointment or 6 months after enrollment for participants who do not attend a screening appointment. Data collected on each questionnaire are shown in Table 1. ASHA call-center staff will administer participant questionnaires over the phone in English or Spanish. Regardless of whether participants complete screening, they will receive US$25 each for the baseline and follow-up questionnaires, and US$30 for the exit questionnaire. Given that compensation is linked only to questionnaires and not to self-collection completion or clinic attendance, screening completion should not be affected by financial motivations.

**Table 1 Tab1:** Questionnaire data collected in the My Body My Test-3 study

	Survey Timing		
	Baseline	Post-intervention	Exit
Sociodemographic data	X		
Knowledge about cervical cancer and screening	X	X	
Perceived likelihood of cervical cancer	X	X	
Worry about getting cervical cancer	X	X	
Embodiment of risk	X	X	
Perceived barriers	X	X	
Self-efficacy	X	X	
Acceptability of and attitudes towards self-collection		X	
Acceptability of and attitudes towards in-clinic screening			X
Patient costs associated with in-clinic screening			X

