### Intervention and control procedures

Women assigned to the intervention arm will receive an HPV self-collection kit by mail, which will include an informational sheet, instructions, and materials to self-collect a cervico-vaginal sample, and a pre-paid envelope to return it by mail (Fig. 1). When HPV self-collection test results are available, ASHA staff will call the participant to deliver her HPV results and schedule her for a free appointment in clinic regardless of the result. Women who with self-collection HPV-positive results will be informed that their results indicate a higher risk for cervical cancer and will be advised to schedule an appointment to complete Pap/HPV co-testing at a study clinic (see results delivery scripts, Additional file 1: Appendix 1). Women with self-collection HPV-negative results will be told that their results indicate lower risk for cervical cancer, but that doctors cannot use self-collection results to make decisions about their care. Participants with both HPV-negative and HPV-positive self-collection results will be able to schedule an appointment for free screening in clinic during the HPV results delivery call. Participants whose self-collection results are inconclusive will be contacted and given the option to try the self-collection again or schedule a clinic appointment. A participant who has not returned a self-collected sample within 3 weeks will receive a mailed reminder letter to return the kit. If the kit still has not been returned 2 weeks later, she will receive a reminder call, at which point she will receive assistance to schedule a clinic appointment if she prefers.

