**Fig. 1 Fig1:**
[figure not shown]
MBMT study flow. ASHA, American Sexual Health Association; HPV, Human papillomavirus; HIPAA, Health Insurance Portability and Accountability Act

Control-arm participants will receive scheduling assistance 1 week after enrollment. This scheduling assistance call provides brief education on cervical cancer and screening, followed by the opportunity to schedule a free screening appointment in clinic for Pap/HPV co-testing. Education will emphasize that cervical cancer is preventable with regular screening and early treatment; the participant is due for screening based on doctor recommendations; and the participant is eligible for free screening at a local clinic. Participants will be directed to go to a study-associated clinic based on residence.

Up to three call attempts will be made to contact a participant to deliver her self-test results or to assist with scheduling a clinic appointment. If these call attempts fail, the study will send a final letter inviting the participant to call the study hotline to receive her HPV self-test results. Participants with HPV self-test positive results who are not reached by phone will receive a letter with their results, strongly recommending screening in clinic.

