To examine possible mechanisms explaining the intervention effect, a standard mediation analysis will be performed by (1) establishing whether the exposure of interest (receipt of HPV-positive result via self-collection) is associated with the outcome (screening in clinic) and mediating variables (e.g., perceived risk), and then (2) determining whether controlling for the mediators meaningfully reduces the size of the association between the exposure of interest and outcome. We will compare completion of screening in clinic in women in the intervention arm who return a self-collected sample and receive a positive HPV self-collection result and in (i) women in the intervention arm who do *not return* a self-collection sample (“non-returners”) and (ii) all women in the control arm, using exact logistic regression (adjusting for baseline covariates and potential confounders). HBM constructs will be evaluated as potential mediators of any observed association. The MacKinnon method will be used to compare coefficients for the intervention-behavior pathway, before and after controlling for the mediator, using the Sobel test [59, 60]. Appropriate methods for handling missing data (e.g., baseline value carried forward or multiple imputation) will be employed to account for unobserved mediator variables. If the intervention is not found to be effective, we will still conduct the mediation analysis to examine suppression (i.e., if the intervention increases one belief but reduces another, these changes could offset one another in how they affect behavior).

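### The mediator questionnaire is timed from the booking call and not from the clinic visit, so a mediator value can be recorded after the outcome it is meant to explain

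*Protocol article*

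**What the plan says.** All references are to the protocol article.

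- **Data collection and measures.** Between the baseline and exit interviews there is one survey: "a follow-up questionnaire 1 week after self-collection result delivery or appointment scheduling call". Table 1 collects the risk constructs at baseline and at this survey, and not at exit.
- **Intervention and control procedures.** Women given a self-collection result, positive or negative, "will be able to schedule an appointment for free screening in clinic during the HPV results delivery call". For the other arm, "Control-arm participants will receive scheduling assistance 1 week after enrollment", and that call also offers a booking. For kits not sent back, "A participant who has not returned a self-collected sample within 3 weeks will receive a mailed reminder letter to return the kit"; then "If the kit still has not been returned 2 weeks later, she will receive a reminder call", with booking help on offer.
- **Primary outcome.** The clock starts at enrollment and runs for 6 months. Attendance at a non-study clinic counts.
- **Analytic approach and power.** HPV-positive women are compared on clinic screening with non-returners and with all controls. Mediation is judged by "determining whether controlling for the mediators meaningfully reduces the size of the association between the exposure of interest and outcome", with a Sobel test. The missing-data sentence deals with mediators that were not observed, by carrying the baseline forward or by multiple imputation.

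**The concern.** The causal chain under test runs from a positive result, through perceived risk, to attendance. Reading a change in coefficient as mediation requires the mediator to be fixed before the outcome occurs. Here the survey is anchored to the call, and the visit has no stated earliest date. A woman seen within days of the call is asked about her risk after she has been examined. Her answer may reflect relief at having attended, or fresh worry, and not the belief that brought her to the clinic.

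Only women who have the outcome can be affected, so the error is tied to the outcome and is not random noise. Its direction is unknown: relief and worry push the mediator–outcome path in opposite directions. The missing-data provision does not help, because a post-visit value is observed and would enter the model.

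At stake is the hypothesis in the Objectives that any effect arises through increased perceived risk. The Discussion names this work as one of the trial's strengths.

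**Working it through.** **1. Scale of the mediation analysis.** Inputs from Power calculations: 510 women at 2:1 (340 and 170), 70% kit return, 13% positivity.

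- HPV-positive women: 340 × 0.70 × 0.13 = 30.9, about 31.
- Non-returners: 340 × 0.30 = 102.
- Fisher exact power for a 30-point difference, 31 v 102, at comparator uptake of 30%, 40% and 50%: 82.6%, 82.8% and 84.6%. The plan states 80–85%, so its figure reproduces. Comparator uptake and a two-sided 5% level are assumptions. Against 170 controls the power is 87–89%.

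These powers concern uptake and do not depend on mediator timing. They confirm that about 31 exposed women is the intended scale.

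**2. Period in which a counted visit can precede the survey.** This takes the mediation outcome to use the same 6-month, any-clinic rule as the primary outcome.

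- Every group: 1 week after the call.
- Controls, from enrollment: 1 + 1 = about 2 weeks.
- Non-returners: 3 + 2 + 1 = about 6 weeks, if the reminder call triggers their survey (the article does not say) and the 3 weeks run from about enrollment.

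The period therefore differs between the groups being compared.

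**3. Number of women.** The share of attenders seen before the survey is not given. Assume 5–30%. Number affected = group size × attendance × early share.

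| Group | Attendance | Early share 5% | Early share 30% |
|---|---|---|---|
| 31 HPV-positive | 50% (assumed) | 0.8 | 4.6 |
| 31 HPV-positive | 75% (assumed) | 1.2 | 7.0 |
| 31 HPV-positive | 95% | 1.5 | 8.8 |
| 170 controls | 45% | 3.8 | 11 × 2.08 = 22.9 |
| 170 controls | 65% | 5.5 | 33.1 |

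The 95% is the highest follow-up that the Background cites from other countries. The 45–65% follows from Power calculations: 60–80% completion less 15 points. In the control arm, completion is clinic attendance.

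**4. What that could do to the mediator path.** In an illustrative simulation, 31 exposed women were compared with 170 controls, with attendance of 75% and 45%. Exposure raised the mediator by 0.5 SD, the mediator had no true effect on attendance, and an early visit lowered the recorded score by 0.5 SD. All of these except the group sizes and the 45% are assumed. Ordinary logistic regression was used, with 1,000 runs per setting.

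| Early share | Mean mediator coefficient | False-positive rate, nominal 5% |
|---|---|---|
| 0% | 0.00 | 6.8% |
| 10% | −0.04 | 4.8% |
| 20% | −0.11 | 11.1% |
| 30% | −0.16 | 20.2% |

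The simulation standard error is about 0.7 points at 5%: √(0.05 × 0.95 / 1000) = 0.007. Up to a 10% early share the effect cannot be told from noise; from 20% it is material. If a visit raised the score instead, the coefficient would be biased upward.

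**The case against.** The layout suggests that the survey was meant to come first. It is separate from the exit interview, and views on clinic screening and visit costs are asked only at exit. One week is short in a 6-month window. These women are long overdue, so unprompted visits before the call may be few. Out-of-sequence records may also be handled in a fuller protocol or analysis plan that is not shown. All of this limits the likely number affected. It does not supply an ordering rule, and survey timing is fixed in this article. A later plan can discard or impute a post-visit value, but it cannot recover a pre-visit one.

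Four stronger readings are tempting and are not supported.

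- **That some values do follow the visit.** No lead time or clinic waiting time is given; they can follow it.
- **That women may already know their co-test result when surveyed.** That would need booking, visit, shipment, laboratory work and reporting within about a week. Nothing in the article indicates such a turnaround.
- **That missed calls widen the gap between call and survey.** The rule "Up to three call attempts will be made to contact a participant" covers results and scheduling calls. A missed one delays the booking made on it and the survey together.
- **That the bias can be sized.** With a true gap of 0.5 SD and a visit effect of −0.5 SD, early shares of 10% and 20% give 0.5 − 0.1 × 0.5 = 0.45 and 0.5 − 0.2 × 0.5 = 0.40 SD. None of these inputs is in the article. The 60–80% in Power calculations cannot stand in for attendance among HPV-positive women, since it counts negative self-tests as complete.

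**Conclusion.** The point holds as a gap in the design. The survey is tied to the call, the visit can be booked on that call, any visit from enrollment counts, and the mediation analysis has no condition that the mediator precede the visit. A post-visit value can therefore enter the model as though it preceded the visit.

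The number of women affected cannot be determined from the article. On the assumptions above it runs from about 1 to 9 of the 31 HPV-positive women and about 4 to 33 of the 170 controls. The consequence runs from negligible at a 10% early share to a false-positive rate of 11–20% at 20–30%.

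A reader might infer that the trial's main result is in doubt. It is not: the intention-to-treat comparison, its sample size and the cost analysis do not use the mediators. The point is worth acting on because the remedy is cheap and the exposed group is small enough for a few reversed records to matter.

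**What to change.** 1. **Data collection and measures:** give the post-intervention questionnaire 1 week after the call or before a booked study-clinic visit, whichever is earlier.
2. **Analytic approach and power:** compare each woman's questionnaire date with her visit date, including non-study visits once these are learned. Report the number with reversed order in each comparison group.
3. **Same section:** add a mediation sensitivity analysis that does not use mediator values recorded after the visit. It could exclude those women, or impute their values with baseline scores and attendance in the imputation model.

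The cost is a call-list rule, a date comparison and one further analysis, with no added contacts. Dates of non-study visits must be collected when attendance is confirmed. Trial status describes recruitment as ongoing, so the first change reaches only women not yet surveyed; the other two cover everyone.

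There are two drawbacks. Early bookers would be surveyed sooner after their result than other women. The values dropped would all come from attenders, and the earliest attenders may differ in perceived risk. That is why the restricted analysis belongs as a sensitivity analysis and not as the main one.

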#### Primary outcome

The primary trial outcome will be completion of cervical cancer screening within 6 months of study enrollment. Screening completion will be defined as screening in clinic or receipt of negative HPV self-collection results. Women with HPV negative self-collection results will be considered screening-complete. Control-arm participants and women with HPV-positive self-collection results will be considered screening-complete if they obtain co-testing or Pap test screening at a study-affiliated or other clinic. Study-associated clinics will report participant clinic attendance directly to the study. Participants who have not attended an appointment at a study clinic will be asked at their 6-month exit questionnaire if they obtained screening at another clinic. If we are unable to reach the participant by phone for the exit questionnaire, we will send emails, texts, and finally a letter to request confirmation whether they attended an in-clinic appointment. If these attempts fail, we will contact other clinics in the participant’s area of residence to determine if the participant attended a screening appointment at another location during these 6 months. Women who undergo screening at any clinic, regardless of whether it is a study clinic, will be considered as having completed the primary endpoint.

#### Secondary outcomes and other measures

Secondary trial outcomes include perceived likelihood of cervical cancer, worry about getting cervical cancer, and embodiment of risk (Fig. 2). These constructs come from the health belief model (HBM) [33], which posits that an increase in the perceived risk of cancer will be associated with increased intention and subsequent completion of cancer screening [32, 56]. Perceived risk has a cognitive aspect, operationalized as *perceived likelihood* of developing cervical cancer, and an affective aspect, operationalized as *worry*. For the present trial, we added an exploratory risk construct, *embodiment of risk,* which is similar to experiential risk in the TRIRISK model, which we operationalize as awareness of and a sense of connection with one’s body as a source of health and risk [57, 58].

**Fig. 2 Fig2:**
[figure not shown]
MBMT model adapted from the health belief model. HPV, Human papillomavirus

We will collect data on costs associated with each arm to estimate the incremental cost per woman screened in the intervention arm as compared to the control arm. Material costs will include those related to training, recruitment, postage, self-collection kit processing, and laboratory testing. Personnel costs will include time spent on staff training, recruitment, mailings, scheduling clinic appointments, and results delivery (Table 2). The study database will automatically generate time stamps to record the time spent by call-center agents on phone calls for self-collection results delivery and appointment scheduling and on failed attempts to complete those calls. Personnel costs will be calculated by total time spent on an activity and the average hourly wage of the agent/staff member completing the activity. Research-specific costs will not be included, such as participant incentives or time spent delivering questionnaires.

**Table 2 Tab2:** Cost data collected in the My Body My Test-3 study

	Cost Perspective	
	Health clinic	Public payers
Training		
Developing and delivering call-center training, study personnel time		X
Training call-center agents, materials		X
Attending call-center training, agent personnel time		X
Recruitment		
Recruitment materials and advertisements^a^		X
Recruitment personnel time^b^		X
Screening identification for eligibility		
Screening calls, personnel time		X
Self-collection for HPV testing		
Non-personnel costs		
Self-collection kits, materials, and postage		X
Processing self-collection kits, laboratory materials		X
Reminder letters, as needed, materials and postage		X
Personnel time costs		
Mailing self-collection kits		X
Delivering self-collection results and scheduling clinic appointments		X
Mailing reminder letters, as needed, materials		X
Clinic services and procedures		
Non-personnel costs		
Processing screening tests, laboratory materials	X	
Personnel time costs		
Scheduling appointment with patient for in-clinic co-testing	X	
Processing/completing paperwork for new patient	X	
Checking patient in and out	X	
Contacting patient who missed appointment	X	
Reporting abnormal screening results to patient and making referral for follow up	X	
Reporting normal screening results to patient	X	
Cost/cost recovery for procedures		
Medicaid reimbursement for screening test	X	X

*ASHA* American Sexual Health Association, *HPV* Human papillomavirus

^a^ Costs include postcards, flyers, yard signs, logo design, newspaper ads, radio station advertisements, website, transportation advertisements, and others

^b^ Costs related to developing and maintaining community partner relationships, direct outreach and recruitment events, distributing recruitment materials, posting advertisements, travel, and administrative procedures

#### Data management and monitoring

All data will be stored in a secure database accessible only to approved study staff. Call-center agents will enter questionnaire data directly into the database during study interviews. Regular checks will be conducted on questionnaire data to identify issues such as inadequate detail obtained from open-ended questions, lack of variation in responses, or unexpected response distribution that might indicate systematic error in data entry. Self-collection and clinic laboratory results will be delivered to study personnel via the Beacon secure results portal and entered by study personnel into the secure database.

#### Confidentiality

Consent forms, HIPAA authorizations, and other paper materials that contain participants’ identifying information will be stored in a locked cabinet accessible only to authorized study personnel. All electronic data will be stored in a secured database and managed by the University of North Carolina (UNC) information technology personnel. All paper records will be destroyed 7 years after the completion of the study. As outlined on the informed consent form (see Additional file 1: Appendix 2), self-collected and clinician-collected samples will be stored de-identified for possible future research.

### Analytic approach and power

Key demographic characteristics (e.g., age, race, marital status, education, income, years since last screening, and travel time between home and clinic) will be compared between study arms to assess any chance imbalances in covariates during randomization. Continuous variables will be analyzed using the Wilcoxon rank sum test, and categorical variables using Fisher’s exact test.

Primary analyses will compare the primary study outcome of screening completion between the study arms, employing the intent-to-treat (ITT) principle, wherein outcomes are analyzed according to study arm regardless of whether the participants complied with the components of the study arm intervention. Using log-binomial regression, the Z statistic for comparison of two binomial proportions will be used to compare the proportion of women in each arm that completed cervical cancer screening and will be reported with 95% confidence intervals based on the normal approximation to the binomial. While we do not expect any baseline covariates to be associated with randomization, we will adjust for any covariates that are associated with randomization and with completion of screening. Such adjustment will account for unexpected chance imbalances in covariates between the trial arms and potentially improve efficiency of inference about the primary outcome. Additionally, to account for potential differential drop-out rates between the two study arms, we will use inverse probability of censoring weights.

Secondary analyses will include per-protocol analyses, where we will assess the effect of the intervention among the subset of study participants who were compliant with their randomization assignment and the study protocol. Exploratory analyses will compare positive HPV detection rates, CIN2+ detection rates, self-collection/clinic-based screening, Pap test participation, follow-up colposcopy and treatment (if indicated), and differential intervention effects by race, age, income, and education level, between the two study arms.

To examine possible mechanisms explaining the intervention effect, a standard mediation analysis will be performed by (1) establishing whether the exposure of interest (receipt of HPV-positive result via self-collection) is associated with the outcome (screening in clinic) and mediating variables (e.g., perceived risk), and then (2) determining whether controlling for the mediators meaningfully reduces the size of the association between the exposure of interest and outcome. We will compare completion of screening in clinic in women in the intervention arm who return a self-collected sample and receive a positive HPV self-collection result and in (i) women in the intervention arm who do *not return* a self-collection sample (“non-returners”) and (ii) all women in the control arm, using exact logistic regression (adjusting for baseline covariates and potential confounders). HBM constructs will be evaluated as potential mediators of any observed association. The MacKinnon method will be used to compare coefficients for the intervention-behavior pathway, before and after controlling for the mediator, using the Sobel test [59, 60]. Appropriate methods for handling missing data (e.g., baseline value carried forward or multiple imputation) will be employed to account for unobserved mediator variables. If the intervention is not found to be effective, we will still conduct the mediation analysis to examine suppression (i.e., if the intervention increases one belief but reduces another, these changes could offset one another in how they affect behavior).

Primary cost assessment will take the perspective of healthcare providers and public payers, who acquire many of the cancer-related screening costs for uninsured and Medicaid-insured women. Costs and a surrogate marker of cervical cancer prevention effectiveness (i.e., women that complete screening) will be measured. The effectiveness measure will have a range of potential values drawn from the trial results, defined by a beta distribution, with costs for each arm defined by a distribution appropriate to the shape of the data. Using Monte Carlo simulation with 10,000 iterations, joint distributions of costs and effectiveness will be estimated for each arm, as well as the proportion of iterations for which HPV self-collection produces the highest net monetary benefit at varying levels of willingness to pay (WTP) [61–63]. Net monetary benefit is defined by the equation (Effectiveness x WTP) - Costs, where the optimal choice will be the intervention that has the highest net monetary benefit at a given value for WTP. For example, at a WTP of US$0, the least expensive option will always be favored, whereas at very high values of WTP, the most effective option will be favored. Given that there is no commonly accepted WTP [64], we will report the net monetary benefit at different potential values of WTP, which will allow decision makers to determine whether to implement self-collection of samples at home for HPV testing in their settings based on their own WTP per woman screened.

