### Randomization and blinding

When the study receives eligible women’s completed consent forms, they will be enrolled into the study and randomized to the intervention or control arm. Randomization will be by permuted block design using blocks of 9 (due to the planned 2:1 ratio for the ratio of intervention to control) [45], stratified by county, using the randomization function of the web programming language hypertext processor (PHP) [46]. We will have a larger intervention group to support analyses of the responses of women with self-collection HPV-positive results. Neither study participants nor study staff will be blinded to the assigned arm. Interviewers will be blinded to study arm for the portion of the post-intervention survey that assesses perceived risk and related psychosocial measures.

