#### Power calculations

A total of 510 participants in a 2:1 randomization ratio of intervention to control provides 88–94% power to detect a 15% or greater difference between arms for the primary outcome, assuming intervention-arm screening completion of 60–80%, which would be consistent with previous studies [47, 65]. A rate of 13% HPV messenger RNA (Mrna) positivity (as detected in MBMT2 using the Aptima HPV assay in the same target population [47]) and a 70% return of kits in the intervention arm will provide 80–85% power to detect a 30% difference in uptake of clinic screening between participants with self-collection HPV-positive results and other subgroups for mediation analysis.

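### Randomization is stratified by county, but the stated primary analysis has no stratum term and picks covariates by observed imbalance and outcome, giving up some precision and leaving the primary model unfixed

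*Protocol article*

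**What the plan says.** Under Randomization and blinding, the protocol article states: "Randomization will be by permuted block design using blocks of 9". The 2:1 allocation is "stratified by county, using the randomization function of the web programming language hypertext processor" (PHP). Participants and setting gives 21 recruiting counties, 12 of them with study clinics.

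Analytic approach and power sets the primary comparison of screening completion as a Z statistic for two binomial proportions, obtained through log-binomial regression; it "will be reported with 95% confidence intervals based on the normal approximation to the binomial". No stratum term is named. Baseline characteristics are compared between arms with Wilcoxon and Fisher tests, and the covariate rule follows: "we will adjust for any covariates that are associated with randomization and with completion of screening". Two aims are given for it: to account for chance imbalances and to "potentially improve efficiency of inference about the primary outcome". Seven characteristics are listed as examples for the baseline comparison, and county is not one of them. No threshold for association is stated.

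Power calculations says that enrolling 510 women at 2:1 "provides 88–94% power to detect a 15% or greater difference between arms for the primary outcome", with intervention-arm completion of 60–80%.

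**The concern.** Three things look wrong together.

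- **The stratum.** Blocking within county removes between-county variation from the arm comparison. An analysis without county does not credit that removal. If county predicts completion, the standard error is too large and the test is conservative. A county effect is plausible here: only 12 of 21 counties have a study clinic, women are directed to a clinic by residence, and clinic attendance is the only way a control-arm woman can complete screening.
- **The selection rule.** After randomization, any baseline difference is chance. Precision comes from covariates that predict the outcome, whether or not they look imbalanced. Requiring imbalance as well discards most of them, which works against the stated efficiency aim. County, balanced by design, would normally fail the first condition.
- **The model is not fixed.** The second condition needs outcome data. With no threshold and an open list, the primary model cannot be known before outcomes are seen, in a trial whose staff are not blinded.

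At stake are some precision and the credibility of the primary result as a pre-specified one.

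**Working it through.** **Inputs from the protocol article.** N = 510 at 2:1, so 340 intervention and 170 control; 15-point difference; intervention completion 60–80%, so control 45–65%; blocks of 9 within 21 counties, or 510/21 ≈ 24 women and 170/21 ≈ 8 controls per county on average; seven example covariates. **Assumed.** Two-sided alpha 0.05 (suggested by the 95% interval), imbalance threshold 0.05, no dropout, and all county and covariate effects.

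**1. The plan's own power.** Continuity-corrected Z test: power = Φ[(δ − c − 1.96·SE₀)/SE₁], with c = ½(1/170 + 1/340) = 0.0044.

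- 60% v 45%: pooled p = 0.55, SE₀ = √(0.55·0.45·(1/170 + 1/340)) = 0.0467, SE₁ = √(0.45·0.55/170 + 0.60·0.40/340) = 0.0465. Φ(1.161) = 87.7%.
- 80% v 65%: SE₀ = 0.0407, SE₁ = 0.0425. Φ(1.549) = 93.9%.

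This matches the stated 88–94%. The figure is for an unadjusted, unstratified comparison.

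**2. County, by formula.** Let county explain a share R² of outcome variance. The true standard error is t = SE₁√(1 − R²), while the unstratified analysis still reports SE₁. Power ignoring strata is Φ[(0.15 − 1.96·SE₁)/t]; power with strata is Φ[0.15/t − 1.96]. At 60% v 45%:

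| R² | Interval too wide by | Type I error, strata ignored | Power, ignored | Power, stratified |
|---|---|---|---|---|
| 0 | 0% | 5.0% | 89.7% | 89.7% |
| 2% | 1.0% | 4.8% | 90.0% | 90.3% |
| 5% | 2.6% | 4.4% | 90.3% | 91.2% |
| 10% | 5.4% | 3.9% | 90.9% | 92.5% |

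**3. County, by simulation.** Blocks of 9 within county, Z test against Mantel-Haenszel. With 21 counties and a between-county SD of 0.5 to 0.8 logits, power was 90.1 to 91.2% ignoring county and 91.2 to 93.2% stratified. With 12 counties it was 90.4 to 91.9% and 91.5 to 93.5%. A further simulation with 21 counties put the unstratified standard error about 2–8% too wide over the same SD range, type I error at about 3–4% in the stronger case, and the power loss at 3 points at most. As a rough ceiling, R² is at most about SD²·p(1 − p): 0.25·0.2475 = 6% and 0.64·0.2475 = 16%, which gives 1/√(1 − R²) − 1 = 3% and 9%.

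**4. The covariate rule.** With seven independent covariates tested at 0.05, the chance that at least one looks imbalanced is 1 − 0.95⁷ = 30%. The simulation used seven independent covariates of equal strength at 60% v 45%, with a robust linear risk-difference model standing in for log-binomial:

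| Log-odds per SD | Power: none / rule / pre-specified | SE: none / rule / pre-specified |
|---|---|---|
| 0 | 88.9 / 88.9 / 88.9% | 0.0469 / 0.0468 / 0.0472 |
| 0.2 | 89.2 / 89.2 / 90.8% | 0.0470 / 0.0467 / 0.0456 |
| 0.35 | 90.0 / 90.6 / 93.5% | 0.0466 / 0.0457 / 0.0431 |
| 0.5 | 89.1 / 89.4 / 95.5% | 0.0462 / 0.0447 / 0.0405 |

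When covariates were prognostic, the rule admitted at least one in about 17–30% of trials. It gained at most 0.6 of a power point over no adjustment. Even at 0.5 it cut the standard error by about 3% (0.0462 to 0.0447), against 12% with pre-specified adjustment. Pre-specified adjustment beat the rule by 1.6, 2.9 and 6.1 points. Type I error under the rule was 4.6–5.3%.

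The 6-point end needs all seven covariates to be strongly prognostic, so a shorter list would gain less. A separate simulation with county (SD 0.5–0.8) and only two covariates (0.4–0.5 log-odds per SD) gave 89.9–90.3% unadjusted and 91.9–94.0% pre-specified, about 2 to 4 points.

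**The case against.** The strongest reply is that the article never excludes county. Log-binomial regression can carry stratum terms, and a condensed article commonly leaves them to the SAP. That stands as far as silence goes: a reader might infer that the plan has decided to ignore county, and the text does not say so. But the covariate rule is stated, not left out. An SAP that follows it would normally leave county out, and an SAP with a fixed model would contradict it. The wording needs changing either way.

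Second, the losses are modest, rest on assumed effects and vanish if nothing is prognostic. For county the error is in the conservative direction. This stands and limits how serious the point is.

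Third, the article claims only a potential efficiency gain, and its first aim is to handle chance imbalance. Adjusting for a prognostic covariate that happens to be imbalanced does correct the realised estimate. This also stands: the rule delivers little efficiency, not none.

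Two stronger readings are tempting. One is that the trial is underpowered; it is not, because the stated power reproduces from an unadjusted comparison and never relied on covariate gains. The other is that outcome-dependent selection inflates the false-positive rate. Simulation of the rule kept type I error near 5%, and association with completion can be judged with the arms pooled. What is shown is discretion over the model, not inflation.

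**Conclusion.** The concern holds in a limited form. The stated analysis does not account for the randomization stratum, and its covariate rule would normally keep county out, recovers little of the available precision and leaves the primary model dependent on observed outcomes.

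Under assumed effects at 60% v 45%, the cost is about 0–3 power points for county and about 0–6 for covariates. These figures assume two-sided 5% testing, no dropout, county SDs up to 0.8 logits and covariate effects up to 0.5 log-odds per SD. The sample size stands. The point is worth acting on because the remedy is inexpensive and makes the primary result harder to challenge.

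**What to change.** In Analytic approach and power, replace the imbalance-and-outcome rule with a primary model fixed before outcomes are examined:

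- arm;
- the randomization stratum, meaning county with sparse counties merged by a fixed rule such as assigned study clinic, or a Mantel-Haenszel analysis over these strata;
- a closed list of covariates already planned for the baseline comparison: age, years since last screening and travel time to clinic.

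Report the standardized risk difference and risk ratio with robust standard errors, and apply the planned censoring weights to the same model. Keep the unadjusted Z comparison, to which the power statement refers, as a sensitivity analysis. Baseline comparisons can remain descriptive but should not choose the model.

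**Cost.** A change to the primary estimator and its wording, with no new data. Sparse counties must be merged, because about 8 controls per county could make a log-binomial model with 21 county terms unstable, and a few degrees of freedom are used. Travel time may overlap with county, so its gain may be small. The article reports recruitment as ongoing, so the model could be fixed at that stage.
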